##### Preliminary Analyses

Once the data set has been cleaned and examined for skewness and missing data, exploratory data analyses will be conducted using univariate methods to describe the variables of interest and bivariate techniques to characterize their interrelationships within our sample. Continuous variables will be summarized over time in each group using means and medians and we will also report their range, interquartile range and standard deviations. Cross tabulated frequencies will be given for all discrete variables by group and time. Both parametric and non parametric correlations will be reported. Results from these descriptive analyses will be used to help guide the primary analyses by providing information about potential problem measures (e.g., heavily skewed distributions) or problematic variable relationships (e.g., highly correlated predictors) and will help determine if transformations of some outcomes (such as percent adherence) are possible in order to use parametric methods. Only after a full descriptive investigation of the dataset has been achieved and potential problem variables identified will primary analyses commence. Potential covariates will be examined prior to final statistical modeling to determine whether there are pre-existing differences between the groups. These exploratory analyses will test for differences in demographic and clinical parameters as well as psychological aspects that have been found to correlate with functioning in our prior work. We will also look at mentored participant outcomes within and across mentors to attempt to determine if there are any discernable patterns of improvement or decline in functioning as a function of clustering of outcomes within mentors or outcomes as a function of each mentor's experience with the protocol. This will help account for therapist effects as well as potential learning and/or fatigue effects. Any variables found to vary significantly by group will be included as covariates in primary and secondary analyses. This will also serve to verify that the randomization was successful.

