Prior to working with actual study patients, the best surrogates for the mentors to practice their new skills with are their fellow mentors, who will all be adolescents with resolved or ongoing recurrent pain problems, whose recent experiences have been similar to those of the mentored participants. Each mentor will participate in several different role-playing exercises during training, in which the mentors will break into pairs and improvise conversations that will occur between mentor and mentored participant. For example, they might be told: "One of you will be the mentored participant who has been to a couple of therapy sessions, but is feeling discouraged, like therapy isn't working and probably nothing is going to help. Talk to your partner and choose a specific therapy. Make up a conversation between the two of you, in which the mentored participant wants to give up on therapy and the mentor responds to those feelings. Remember what you have learned about cognitive-behavioral principles in thinking about what the mentor should say." These mock conversations will be observed and critiqued by trainers. Each mentor will be assigned to no more than three mentored participants at any one time; some mentors will only work with one mentored participant during some cycles, to ensure they can take on a mentored participant if one of the group becomes ill or has another emergency. (Additional mentors may be trained during the intervention period if needed due to attrition or higher than anticipated subject enrollment.) During the period of active mentorships (about 18 months), mentors will meet monthly with the research team to review guidelines, provide feedback, and discuss problems that may arise. Mentors will participate in the ongoing iterative process of reviewing and refining the protocol after each cycle.]

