### Intervention

Each mentored participant will be assigned to a peer mentor. Each mentor will work with no more than three subjects at one time; once all mentors have been assigned one to three subjects, recruitment will stop until the intervention cycle concludes. Cycles may be staggered depending on recruitment and mentor availability.

Each cycle will consist of 10 sessions of 30-60 minute phone calls conducted over a period of eight weeks. The mentor and mentored participant(s) will have two sessions per week for the first two weeks, and one session per week for the remaining six weeks. Current literature supports the use of an expanding-interval schedule of interventions (compared to a massed (single session) or uniform-interval schedule) with evidence that the expanding schedule may help to attenuate long-term recurrence of negative emotions [37]. Phone calls will take place on a secured, monitored conference call line so that no participants will exchange personal contact information. The time of all phone meetings will be scheduled by the research staff, based on availability of mentor and mentored participant(s) and will remain at a fixed time each week. Mentoring sessions will occur only during the scheduled times and mentored participant-mentor contact outside of the mentoring sessions will be specifically prohibited. During each session, participants will also be viewing a slide presentation at the time of the conference call, so that didactic information can be presented. This presentation has been developed by doctoral-level research staff. As previously mentioned, to ensure safety of all participants, a member of the research team will be monitoring all telephone calls. This individual will facilitate the discussion, only if necessary, as well as intervene in any potential safety concerns (e.g., discussion of suicidal ideation) or inappropriate behavior (e.g., bullying).

In an effort to increase adherence, mentored participants will be informed that if they miss two consecutive mentoring sessions, or miss three sessions total over the course of the intervention for non-emergency reasons, they will be removed from the study. Additionally, peer mentors who miss two mentoring sessions (for non-emergency reasons) will be removed from further participation as a mentor. Mentored participants will then be reassigned to a new mentor for the remaining sessions.

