We expect to recruit 4 - 6 mentored participants for each two-month cycle during the active intervention period of 16 months, yielding approximately 32 - 48 mentored participants, with a corresponding number of controls, and seven mentors, giving a total study enrollment number of 70 - 100.

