##### Primary Analyses

The primary outcomes are adherence (percent of sessions attended, percent of home exercises completed). The primary analysis method is repeated measure analysis of variance (ANOVA) between the two groups or the non parametric equivalent (Friedman procedure). We will subtract baseline value from the 2- and 4-month assessment values and use residualized change scores from baseline as the outcome. We will use the Tukey-Fisher criteria for post hoc mean/median comparisons under the ANOVA or Friedman model. The same methods will be used for the analyses on NRS and FDI scores.

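### Mentored participants are clustered within about seven mentors, but the primary ANOVA has no mentor term and clustering is only inspected, so standard errors are too small if mentors differ

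*Protocol article*

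**What the plan says.** - **Number of mentors.** The sample size section (Sample Size Determination and Power Analysis) describes recruitment "yielding approximately 32 - 48 mentored participants, with a corresponding number of controls, and seven mentors".
- **Load per mentor.** Under Intervention: "Each mentor will work with no more than three subjects at one time". Mentors serve over repeated cycles, so the total per mentor exceeds the number held at one time.
- **Changes of mentor.** Peer Mentor Training allows for more mentors: "Additional mentors may be trained during the intervention period if needed due to attrition or higher than anticipated subject enrollment". Under Intervention, mentors who miss two sessions for non-emergency reasons are removed. The text continues: "Mentored participants will then be reassigned to a new mentor for the remaining sessions".
- **Handling of clustering.** Only Preliminary Analyses mentions it. The team will look for "any discernable patterns of improvement or decline in functioning as a function of clustering of outcomes within mentors", and for effects of each mentor's growing experience, and says this helps account for therapist effects. The only stated route from that step into the later models is that variables differing significantly between groups become covariates.
- **Primary model.** Under Primary Analyses: "The primary analysis method is repeated measure analysis of variance (ANOVA) between the two groups", with Friedman as the non-parametric alternative. The same methods apply to NRS and FDI, and Secondary Analyses uses them for anxiety and depressive symptoms. No mentor effect is named.

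**The concern.** The design is partially nested. Outcomes in the mentored arm share a mentor; each control stands alone. If mentors differ in how well they engage, explain or encourage, outcomes of participants with the same mentor are correlated. The mentored-arm mean then varies more than a two-group ANOVA assumes.

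The protocol recognises this and offers inspection as the answer. Inspection leaves the standard error as it was. The covariate route cannot carry mentor into the model either, because mentor exists in one arm only and cannot be compared between groups.

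Two things are at stake. Confidence intervals and p-values for mentoring would be too favourable. And the inference would treat the particular mentors as fixed, whereas the larger trial planned in the Discussion needs to know what a program of trained peers does and how much mentors vary.

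**Working it through.** **Inputs from the protocol.** Seven mentors; 32 to 48 mentored participants with a matching number of controls; 29 per group in the power calculation; standardised effect 0.52; two-sided alpha 0.05; power 0.80.

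**Assumption.** The protocol gives no ICC for mentors. The range 0.01 to 0.20 is assumed.

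**Step 1: the plan's own figure.** For two independent means, n per group = 2 × (1.960 + 0.842)² / 0.52² = 58.05, rounded up to 59. The stated 29 is not reproduced. That is a separate and larger problem. What matters here is that neither figure contains a clustering term.

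**Step 2: cluster size.** m = 29/7 = 4.14, 32/7 = 4.57, 48/7 = 6.86.

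**Step 3: inflation.** In the mentored arm the design effect is DE = 1 + (m − 1) × ICC; in the control arm it is 1. With equal arms, true SE / assumed SE = √((DE + 1)/2). Actual two-sided type I error ≈ 2 × [1 − Φ(1.960 / ratio)]. The between-group test in a repeated-measures ANOVA works on participant averages, so the same arithmetic applies to it.

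Worked example, 48 per arm, ICC 0.10: DE = 1 + 5.86 × 0.10 = 1.586; ratio = √(2.586/2) = 1.137; SE too small by 1 − 1/1.137 = 12.1%; type I error = 2 × [1 − Φ(1.960/1.137)] = 8.5%.

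| Per arm | ICC | DE | SE too small by | Type I error |
|---|---|---|---|---|
| 29 | 0.01 | 1.03 | 0.8% | 5.2% |
| 29 | 0.05 | 1.16 | 3.7% | 5.9% |
| 29 | 0.10 | 1.31 | 7.0% | 6.9% |
| 29 | 0.20 | 1.63 | 12.8% | 8.7% |
| 32 | 0.01 | 1.04 | 0.9% | 5.2% |
| 32 | 0.05 | 1.18 | 4.2% | 6.0% |
| 32 | 0.10 | 1.36 | 7.9% | 7.1% |
| 32 | 0.20 | 1.71 | 14.2% | 9.3% |
| 48 | 0.01 | 1.06 | 1.4% | 5.3% |
| 48 | 0.05 | 1.29 | 6.6% | 6.7% |
| 48 | 0.10 | 1.59 | 12.1% | 8.5% |
| 48 | 0.20 | 2.17 | 20.6% | 12.0% |

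Simulated t-tests (40,000 trials per setting, seven mentors, no treatment effect) agreed with the last column to within 0.5 percentage point.

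**Step 4: can inspection clear the issue?** Take a formal one-way F test across seven mentors at the 5% level as a generous version of looking for patterns. Simulated over 29 to 48 mentored participants, it detects clustering in about 10% to 14% of trials at ICC 0.05, 16% to 27% at 0.10 and 32% to 53% at 0.20. At ICC 0.05 to 0.10, finding nothing is the usual result even though clustering is present.

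**Step 5: power and sample size.** For effect 0.52 and 48 per arm, power with a correct standard error is 0.72 at ICC 0, 0.66 at 0.05, 0.61 at 0.10 and 0.53 at 0.20. For 80% power, n per arm = 58.05 × (DE + 1)/2. With m held at 4.57 to 6.86, this gives 64 to 67 at ICC 0.05 and 69 to 76 at 0.10, against 59 without clustering.

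**The case against.** The strongest reply is that the protocol does not say clustering will be ignored. It names the issue, says descriptive results guide the primary analyses, and may leave the model to an analysis plan that is not shown. Degrees-of-freedom methods and variance structures do commonly belong there. But the article does fix a primary model, without mentor, and does state what the inspection achieves. Those two statements do not fit together, and no step connects them.

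Second, everything depends on an unknown ICC. This stands: at 0.01 the effect is negligible. A common manual, joint training, staff-prepared slides and monitoring of every call may hold mentor variation down, though the protocol does not quantify this.

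Third, seven is not a fixed number, because more mentors may be trained. This softens the problem without removing it. With 48 per arm and ICC 0.10, 12 mentors give m = 4, DE = 1.30, ratio √1.15 = 1.072 and type I error of about 6.8%, against 8.5% with seven.

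Fourth, this is an exploratory pilot that admits it may be underpowered. That limits the severity. It does not excuse the standard error, because the protocol sets out two-tailed tests at the 0.05 level.

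Finally, with about seven mentors the ICC estimate will be imprecise and may well be zero. That is true, and it is a reason to fix the model in advance instead of letting the data decide whether mentor enters.

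**Conclusion.** The concern holds. For any positive within-mentor correlation, the stated primary and secondary analyses give standard errors that are too small, and the planned inspection neither corrects this nor can be relied on to reveal it. Assuming seven mentors and an ICC of 0.05 to 0.10, type I error is about 6% to 7% at 29 per arm and 7% to 8.5% at 48 per arm; at ICC 0.20 it is about 9% to 12%. At ICC 0.01 the effect is trivial. These sizes rest on the assumed ICC, near-equal mentor caseloads and no increase in the number of mentors. This should be changed, but it ranks below the separate discrepancy in the 29-per-group figure.

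**What to change.** Replace the two-group ANOVA, for primary and secondary outcomes, with a prespecified partially nested mixed model:

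- a random mentor effect in the mentored arm only, with each control as a cluster of one;
- separate residual variances by arm;
- Satterthwaite or Kenward-Roger degrees of freedom;
- participants classified by first assigned mentor, which settles the analysis of those later reassigned;
- the mentor term kept whatever the preliminary inspection shows.

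Report the mentor ICC with its interval as a pilot result for the larger trial. Keep the plots by mentor and by mentor experience as description, and drop the statement that they account for therapist effects. Any revised sample size should carry the design effect over a stated ICC range.

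The cost is analysis wording and code; no data collection or trial procedure changes. Intervals become somewhat wider and degrees of freedom few with seven mentors. Validity does not suffer: a simple cluster-mean comparison with Satterthwaite degrees of freedom kept simulated type I error near 5% with seven mentors at every ICC tried, including zero.

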## Methods/Design

### Sample

#### Mentored and Control Subjects

All potential participants must be patients of the UCLA Pediatric Pain Program. During the first visit (prior to being offered study participation), all clinic patients are given a thorough medical evaluation and are recommended specific therapies to help with various skills to manage their pain. Any English-speaking patient between the ages of 12 and 17 diagnosed with a chronic pain disorder at the UCLA Pediatric Pain Program, or referred with this diagnosis, is eligible to be a subject for the study. Participants must have access to a computer connected to the internet, as well as a telephone in order to participate in the mentoring and complete measures administered online. Other than age, the only exclusions are out-of-area patients seen for consultation only before referral back to local providers or patients with another physical or psychological condition that, in the judgment of the principal investigator (PI), would make it difficult to participate.

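### Covariates for the primary and secondary models are picked by significance tests of baseline imbalance, and the change-score outcome they feed is loosely defined

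*Protocol article*

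**What the plan says.** The Preliminary Analyses section sets out a screening step: "Potential covariates will be examined prior to final statistical modeling to determine whether there are pre-existing differences between the groups". On its scope it says: "These exploratory analyses will test for differences in demographic and clinical parameters as well as psychological aspects", the last of these being aspects that correlated with functioning in the team's earlier work. The rule that follows is "Any variables found to vary significantly by group will be included as covariates in primary and secondary analyses", and the section then claims: "This will also serve to verify that the randomization was successful". It names no covariate that enters regardless of the test result, and it gives neither the number of variables nor the significance level for the screen.

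The Primary Analyses section says "The primary outcomes are adherence (percent of sessions attended, percent of home exercises completed"). The outcome is then built in one sentence: "We will subtract baseline value from the 2- and 4-month assessment values and use residualized change scores from baseline as the outcome". Pain and disability follow the same route: "The same methods will be used for the analyses on NRS and FDI scores".

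Three other places bear on adherence:
- The section on mentored and control subjects says: "During the first visit (prior to being offered study participation), all clinic patients are given a thorough medical evaluation and are recommended specific therapies".
- The Primary Outcomes section describes the tracking form as a weekly count of attended and missed clinician appointments, with use of other therapies and medication. It does not mention home exercises.
- Table 1 marks treatment tracking at baseline as well as at later time points.

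**The concern.** In a randomised trial, the null hypothesis of a baseline test is true by design if allocation was carried out properly. A significant result is then a chance event, and a non-significant one does not confirm that allocation was sound. Nor does the p-value say whether a variable predicts the outcome, which is what makes a covariate worth having. A strong predictor that is balanced by luck is left out; an irrelevant variable that is unbalanced by luck is put in. The primary model therefore cannot be written down before the data are seen.

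The outcome sentence adds a second uncertainty. Follow-up minus baseline and residualised change are different quantities with different variances. Two analysts could follow the text in good faith and report different results for pain and disability.

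For adherence, either construction needs a baseline percentage, and the article does not say what that would be a percentage of.

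**Working it through.** The plan gives no figure for this point, so there is none to reproduce.

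**Inputs from the protocol.** Randomisation in blocks of 4 to equal groups (Randomization). Two-sided alpha 0.05, standardised effect 0.52 and 29 per group (Sample Size Determination and Power Analysis). The 29 is used below only as a simulation size; whether it is adequate is a separate matter.

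**Assumptions, not in the protocol.** Number of screened variables k = 5, 10 or 15; independent tests, each at 0.05; correlation r between baseline and follow-up = 0.3, 0.5 or 0.7.

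**Step 1: how often chance changes the model.** P(at least one covariate enters) = 1 − 0.95^k.
- k = 5: 1 − 0.774 = 0.226
- k = 10: 1 − 0.599 = 0.401
- k = 15: 1 − 0.463 = 0.537

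**Step 2: what the rule costs.** A simulation used 29 per arm, one follow-up value, one covariate with correlation r to the outcome, effect 0.52 and 10,000 runs per setting.

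| Analysis | r = 0.3 | r = 0.5 | r = 0.7 |
|---|---|---|---|
| Power, adjust only if imbalance is significant | 0.48 | 0.50 | 0.50 |
| Power, always adjust | 0.52 | 0.61 | 0.78 |
| Type I error, adjust only if significant | 0.046 | 0.044 | 0.037 |
| Type I error, always adjust | 0.047 | 0.049 | 0.049 |

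The screening rule forgoes nearly all the gain from adjustment, because the covariate enters in only about 5% of trials. Type I error is at or below the nominal level.

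**Step 3: the two readings of the outcome sentence.** With equal variances, raw change has variance proportional to 2(1 − r) and ANCOVA to 1 − r². The ratio is 2(1 − r)/(1 − r²) = 2/(1 + r).
- r = 0.3: 2/1.3 = 1.54
- r = 0.5: 2/1.5 = 1.33
- r = 0.7: 2/1.7 = 1.18

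In the same simulation, with baseline as the covariate, power at r = 0.3/0.5/0.7 was:
- raw change: 0.37/0.50/0.72
- residualised change: 0.52/0.61/0.77
- ANCOVA: 0.52/0.61/0.78

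The mean residualised estimate was about 0.51, against a true 0.52. The attenuation has a simple source. When the residualising regression has no group term, the group coefficient equals the ANCOVA coefficient times (1 − c²), where c is the sample correlation of group with baseline. With 58 participants, c² averages 1/57 = 0.018 under randomisation, and 0.52 × 0.982 = 0.511.

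**Step 4: adherence, passages side by side.** Table 1 schedules tracking at baseline, and therapies are recommended before study entry is offered, so some pre-enrolment record may exist. But the article gives no look-back period and no denominator, and home exercises, which are half of the stated primary outcome, are not in the form as described. A newly referred patient with no appointment yet due has zero in the denominator and so no percentage to subtract.

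**The case against.** The strongest defence concerns the outcome sentence. Read in sequence, it is one procedure: form the difference, then residualise it on baseline. With Y the follow-up and X the baseline value, the residuals of Y − X regressed on X are those of Y regressed on X, since Y − X − a − (b − 1)X = Y − a − bX. On that reading the named outcome already adjusts for baseline. This stands. A reader might infer that the plan has no baseline adjustment, or that it needs 33% to 54% more participants; the text supports neither. Those percentages belong to raw change at r = 0.5 and 0.3 only, and the excess falls to 18% at r = 0.7.

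A reader might also infer that adherence cannot have a change score, or that the primary analysis cannot be computed. Table 1 contradicts this by scheduling tracking at baseline. What remains is that the baseline percentage is undefined and may be empty for some patients.

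On the covariate rule, it can be said that the psychological candidates were chosen because they correlated with functioning in earlier work, so part of the pool is prognostic. That is fair, but it argues for including them whatever the imbalance test shows. It is also fair that the simulated power loss applies where the covariate is the only adjustment. If the outcome is already residualised on baseline, the loss from omitting a further covariate depends on what it adds, which the protocol does not tell us.

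Finally, a reader might infer a false-positive problem, or judge the matter at 50 to 60 participants. The simulation shows no type I error inflation. The sample-size text gives a minimum of 50, but also expects 32 to 48 mentored participants with matching controls, that is 64 to 96. The trial is described as an exploratory pilot, which lowers the stakes but does not make a chance-driven model useful.

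**Conclusion.** The covariate rule is a stated fault, not a detail left to another document. It lets chance imbalance determine the primary and secondary models and presents the tests as a check they cannot provide. The 23%, 40% and 54% measure how unstable the model is, not bias or error, and they rest on an assumed number of independent tests at 0.05. The harm is loss of precision and an unfixed model.

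The outcome sentence is ambiguous rather than self-defeating. The cost ranges from almost nothing (residualised change) to the raw-change variance penalty, which depends on a correlation the documents do not give. The adherence point is limited to an undefined baseline percentage. All of this should be corrected before the analysis.

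**What to change.** - Delete the rule that brings in covariates by significance of group differences, and the sentence on verifying randomisation. Show baseline characteristics by arm descriptively, without tests.
- Fix one baseline-adjusted model in advance for FDI, NRS, RCADS and CASI: the 2- and 4-month values on group, time, group-by-time and the baseline value of the same outcome. Add, if wanted, a short list of prognostic covariates named beforehand and kept whatever their balance. This replaces the outcome sentence and removes both the ambiguity and the slight attenuation.
- For adherence, compare arms on the on-study percentage without subtracting baseline, unless a baseline measure is defined with its period, its denominator and a source for home exercises.

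The cost is analysis wording only. Table 1 already schedules all four scales at baseline, so no new data are needed.
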